### ***Intervention impact outcomes***

The primary outcome of the intervention is 1) CoC completion rate of mothers and infants. Secondly, outcomes such as 2) the PNC rate within 48 hours postpartum, 3) the rate of complications requiring hospitalization of mothers and their infants for more than 24 hours, and 4) the perinatal mortality ratio (PMR) will be measured. All the data will be compared between intervention and control arms.

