### **Study Population**

Pregnant women will be recruited as participants of the study from the areas of Dodowa, Kintampo and Navrongo HDSS. Eligibility criteria will be as follows.

(i) Participants of the baseline survey:

Study population would be females who got pregnant in the target HDSS sites. The inclusion criteria are those who gave birth within the two years preceding the baseline survey, including live-births and still-births. The exclusion criteria will be those who have infants younger than six weeks of age at the beginning of the data collection.

(ii) Participants of the intervention and evaluation survey:

The study population would be females who got pregnant in the target HDSS sites. The inclusion criteria will be those who are between 16 weeks gestation and six weeks postpartum during the intervention period of A-1, B-1 and B-2 **(1st October 2014 to 31st December 2015)** including live-births and still-births. The exclusion criteria will be those who have infants younger than six weeks of age at the beginning of the data collection. From preliminary information gathered from the participating three HDSS sites, during the intervention period, about **27,500** mothers are expected to experience pregnancy, delivery, or the postnatal period in the study sites, and these will form the target population in this study. **An**

estimated total of 10,000 mothers are expected to be fully followed up from their first ANC visit to their PNC visit at six weeks post-partum (approximately 5,000 intervention and 5,000 control arms), which accounts for 36 % of all target mothers. The remaining 64% will be also followed up as they will partially receive the intervention; those who registered at their first ANC before the start of intervention, and those whose third PNC period occurs after the intervention period. See table below.

| Year                 | 2014          |   |   |   |   |   |   |                |    |    |   |   | 2015 |   |   |               |   |   |   |    |    |    |  |  |
|----------------------|---------------|---|---|---|---|---|---|----------------|----|----|---|---|------|---|---|---------------|---|---|---|----|----|----|--|--|
| Month                | 3             | 4 | 5 | 6 | 7 | 8 | 9 | 10             | 11 | 12 | 1 | 2 | 3    | 4 | 5 | 6             | 7 | 8 | 9 | 10 | 11 | 12 |  |  |

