***(B-1) 24-hour retention of mothers and their infants after delivery***

Upon delivering, women will be encouraged to stay at the health facilities for at least 24 hours with their neonates to receive PNC. The aim of this intervention is to improve the within-48-hours-postpartum PNC uptake rate of mothers and neonates. The implementation period will run from **October 2014 to December 2015**. This intervention will be conducted only in those health facilities providing delivery service by SBAs and having space for abed for postpartum rest. Approximately 5,850 women are estimated to

use this service during the intervention period. For those who are not fully followed from the first ANC to the PNC at six weeks postpartum, the impact of CoC completion will be analyzed according to the care stages they received during the intervention period. Such data may be analyzed separately from fully followed-up mothers. Intervention impacts in terms of postpartum complications will also be analyzed.

In this intervention, mothers and babies will receive necessary care in the health facility for 24 hours after delivery. During their stay, mothers will be provided nutritious food drink (Milo) offered by the Ghana EMBRACE implementation research project. After ensuring all of the necessary health check points, health service providers will discharge the mothers. In cases where mothers and/or neonates have particular symptomatic complications, midwives will provide supplementary extended care or refer to the district hospital, as appropriate. The women will be advised to come to the health facilities with their neonates for PNC on the seventh day and at the end of six weeks following delivery. If the women do not return to the health facility for PNC as instructed, the health workers will visit their homes to provide PNC service, as part of their routine follow-up duties.

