## **Impact Evaluation**

To evaluate the impact of the intervention package, the baseline and evaluation surveys will be conducted in three HDSS sites. The period of the baseline survey will be from July to August 2014. **The intervention period will run from October 2014 to December 2015. Period of the last three months (October to December 2015) will be added to mitigate the decline in the service quality due to the abrupt intervention cessation. The evaluation survey period will be from October to November 2015, and the survey's target will not include the mothers who would newly enter this period, thus the survey results would not be influenced by the addition of the period.**

Individual mother- and infant-level data will be collected regarding their CoC MNCH completion rates, complication rates, within-48-hours-postpartum PNC rates, mortality and adverse outcomes. In the baseline survey, data will be collected through household surveys of mothers who delivered within the two years preceding the survey. In the evaluation survey, mothers will be included if they have received any aspect of MNCH care, even in part, during the intervention period. However, for data from those who cannot be fully followed up during the intervention period, analyses will be performed according to the care stages they received during the intervention period. This may be analyzed separately from mothers who have passed the period from the first ANC session to the PNC at six weeks during the intervention period. Individual mother- and infant-level data will also be obtained from the HDSS data set regarding pregnancy outcomes

and morbidity.

To evaluate the impact of the implementation, a set of data and supporting information will be collected during the supervision by the DHMT/SDHMT. **This includes the status of CoC card distribution and actual users, as well as uptake of PNC within 48 hours postpartum, either by retention of mothers at the facilities or by home visits. In addition, qualitative data of women and health workers will be collected during the monitoring by the researchers. Those include transcript data of interview, audio-visual data (photographic and motion data) which will be collected through the in-depth interviews. Target of in-depth interview will be women and health workers who will be involved in the intervention or control arm.**

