### **Statistical Analysis**

Baseline and evaluation survey data will be analyzed to assess changes in each outcome in both intervention and control arms. To minimize overestimation of the intervention effect, all intervention impact outcomes will be estimated by intention-to-treat analysis, by which individuals are analyzed according to an allocated arm as the outcome data are

available, regardless of the place where they received the care. Also, all eligible individuals are included in the analysis, whether or not they provided outcome data.

Data collected at the individual level will be analyzed using generalized estimating equations (GEE) and mixed effects models for both continuous and binary outcomes.

Adjustment factors include items such as basic demographic characteristics and socio-economic characteristics, as well as the characteristics of facilities located in the area where the mother and infant live. Data analysis will be done primarily using Stata version 12.1. (StataCorp LP, College Station, Texas, USA).

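### Analysing partly followed mothers by the care stages they received, and surveying only mothers who received care, conditions the arm comparison on uptake

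*Protocol*

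**What the plan says.** The primary outcome is completion of the continuum of care (CoC): at least four antenatal (ANC) visits, skilled delivery and three postnatal (PNC) contacts. The PNC rate within 48 hours is the next outcome listed. Both are compared between arms.

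Study Population expects 10,000 of 27,500 target mothers to be fully followed. Of the others it says: "The remaining 64% will be also followed up as they will partially receive the intervention". They are defined by calendar timing: "those who registered at their first ANC before the start of intervention, and those whose third PNC period occurs after the intervention period".

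For these mothers, Impact Evaluation states that "analyses will be performed according to the care stages they received during the intervention period". The section on intervention B-1 repeats the rule for the primary outcome: "the impact of CoC completion will be analyzed according to the care stages they received during the intervention period". Separate analysis is optional: "This may be analyzed separately from mothers who have passed the period from the first ANC session to the PNC at six weeks".

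Impact Evaluation also sets entry to the evaluation survey: "mothers will be included if they have received any aspect of MNCH care, even in part, during the intervention period".

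Statistical Analysis calls for intention to treat by allocated arm and adds that "all eligible individuals are included in the analysis, whether or not they provided outcome data".

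**The concern.** The package is meant to turn missed contacts into received ones, so receipt of care is the outcome. If receipt also decides which stages are analysed, or which mothers are surveyed, the comparison is restricted to women in whom the package, or usual care, has already worked.

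The stage rule can be taken in two ways. It may set the denominator, in which case missed stages drop out. Or it may group women by the stages they received, in which case the arms are compared within groups formed after randomisation and shaped by the intervention. Neither estimates the effect of allocation on uptake.

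The survey rule adds a second filter. A mother who was pregnant or newly delivered in the period but received no care is eligible under Study Population, yet is left out of the survey. She is a non-completer, and if the intervention works there should be more such women in the control arm.

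**Working it through.** **Inputs from the protocol.** 27,500 target mothers, 10,000 fully followed, 36% and 64% (Study Population); groups of 8,750, 10,000 and 8,750 by month of conception (Figure 2); the CoC components (Background); one third of pregnant women in Kintampo not delivering in a facility (Study Setting).

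**Assumptions, not in the protocol.** Equal split between arms; the Kintampo facility figure as a proxy for skilled delivery in controls; 75% to 80% skilled delivery under intervention; the contact rates in step 4; contacts independent within a woman.

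**1. The protocol's own figures.** 8,750 + 10,000 + 8,750 = 27,500. 10,000/27,500 = 36.4% and 17,500/27,500 = 63.6%. The stated 36% and 64% are reproduced.

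**2. How many of the 17,500 matter for delivery and 48-hour PNC.** Figure 2 runs from March 2014 to December 2015, which is 22 months. 27,500/22 = 1,250 conceptions a month, so 8,750 is 7 months and 10,000 is 8 months. The last group therefore conceives from June to December 2015. A June 2015 conception reaches term about nine months later, around March 2016, after the intervention ends in December 2015. That leaves about 8,750 partly followed mothers for these two items, or 4,375 per arm.

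**3. Single-contact items.** With n mothers due and a proportion p receiving the contact:
- due basis: np/n = p
- received-only basis: np/np = 100%, whatever p is.

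For skilled delivery at 66.7% in controls against 75% to 80%, the true difference is 8.3 to 13.3 points. On the received-only basis it is 100% against 100%, a difference of 0. Mothers dropped: 4,375 × 1/3 = 1,458 in controls, against 4,375 × 0.25 = 1,094 down to 4,375 × 0.20 = 875 under intervention.

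**4. Multi-contact blocks.** Suppose a block counts as received after at least one contact. Completion of three PNC contacts is p³ on the due basis and p³/(1 − (1 − p)³) on the received basis.

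| Contact rate, control / intervention | Due basis | Difference | Received basis | Difference |
|---|---|---|---|---|
| 0.4 / 0.6 | 6.4% / 21.6% | 15.2 | 8.2% / 23.1% | 14.9 |
| 0.5 / 0.7 | 12.5% / 34.3% | 21.8 | 14.3% / 35.3% | 21.0 |
| 0.7 / 0.85 | 34.3% / 61.4% | 27.1 | 35.3% / 61.6% | 26.4 |

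For at least four ANC visits out of an assumed six opportunities, at 0.5 against 0.6, completion is 34.4% and 54.4% on the due basis, and 34.9% and 54.7% on the received basis. The difference is about 20 points either way. If contacts cluster within women, more women have none at these rates, so a small distortion is not guaranteed.

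**5. Three records, with delivery and three PNC contacts all due.**

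| Mother | Received-only, by contact | Received-only, by block | Due basis |
|---|---|---|---|
| A: skilled delivery and 48-hour check | 2 of 2 | delivery complete; PNC 1 of 3 | 2 of 4 |
| B: six-week visit only | 1 of 1 | delivery dropped; PNC 1 of 3 | 1 of 4 |
| C: home delivery, no PNC | undefined | dropped from both | 0 of 4 |

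If Mother C also had no ANC in the period, the survey rule excludes her altogether.

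**6. The sections side by side.** Study Population admits by gestation and postpartum timing. Statistical Analysis keeps every eligible individual in the allocated arm. Impact Evaluation and B-1 select by care received. An analyst cannot follow all of them as worded.

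**The case against.** A reader might infer that stage completion will score 100% in both arms throughout, or that the trial's main result is lost. The protocol does not support that. It defines no denominator and no received-over-received score. The collapse follows only for single contacts. If ANC and PNC are blocks, as the component list suggests, completion stays below 100% and the arm difference hardly moves in step 4. The 10,000 fully followed mothers are not under the stage rule.

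The sensible reading also has support. Partial follow-up is defined by calendar timing, not by missed care. The Rationale reports a sharp fall in uptake at the 48-hour PNC stage, which could not be seen if only receivers were counted. The 48-hour rate is itself an outcome compared between arms. The sponsor probably meant the stages that fell inside the period. The figure of 17,500 is also too large for delivery and 48-hour PNC.

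All of that stands, and it limits the size of the point. It does not remove it. The Rationale calls the single 48-hour contact a stage, so the contact-level reading is open for the very item that B-1 and B-2 target. The survey rule separately conditions on receipt, so this is not one stray word. Nor is it detail that can be left to an analysis plan: the protocol states a rule that a later plan would have to follow or contradict.

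**Conclusion.** The point holds as a conflict in the stated rules. Read literally, the stage rule and the survey rule both condition on uptake, against the protocol's own eligibility and intention-to-treat rules.

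- The stage rule formally governs 17,500 of 27,500 mothers (64%), of whom about 8,750 bear on delivery and 48-hour PNC. The latter figure takes Figure 2's months of conception at face value.
- For those two items, a received-only denominator would bring any true difference to zero. This does not depend on the assumed rates.
- For ANC and PNC blocks the loss may be small: under one point in the PNC scenarios shown, which assume independent contacts.
- The primary result is exposed to the stage rule only if partly and fully followed mothers are pooled, which the optional wording allows. The survey rule is not limited to partly followed mothers. The protocol gives no figure for women with no care, so its effect cannot be sized.

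**What to change.** 1. In Impact Evaluation and in the B-1 section, replace the reference to stages received with *the care stages that fell due during the intervention period, whether or not received*.
2. Decide which stages are due from conception or gestation and delivery dates only. The denominator for a stage is every eligible mother in the allocated arm for whom it fell due, and a contact not received counts as not completed.
3. Change the survey-inclusion sentence in Impact Evaluation to eligibility by pregnancy or postpartum timing, as in Study Population. Without this, women with no care stay excluded even after the first two changes.
4. Check that Study Population, B-1, Impact Evaluation and Statistical Analysis then agree.

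The cost is three sentences of wording, plus identifying mothers for the survey by timing rather than by receipt of care. The surveillance system already records pregnancies and births. Reported stage rates will be lower.

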## **METHODS**

### **Study Setting**

The study will be carried out at three different Health and Demographic Surveillance System (HDSS) sites of the GHS in Ghana: Dodowa (Greater Accra region), Kintampo (Brong-Ahafo region), and Navrongo (Upper East region). See figure 1. These three sites were selected based on the high reliability of HDSS data for evaluating the study's impact. The feasibility of implementation will be evaluated in different contexts. The HDSS involves a semi-annual recording of vital demographic events, including pregnancies, births, deaths, and migration, occurring among residents of all households in the HDSS area. Other data are also collected and updated regularly, such as household characteristics, morbidity, and vaccination uptake.

The Dodowa HDSS site registered a surveillance population of approximately 115,000 as of 2011. The site is located only about 40 kilometers away from Accra. Consequently, pregnant women of this site often prefer to access health facilities in Accra to give birth. Delivery of services is, however, generally challenging due to the large land size, covering about 40.5% of the Greater Accra Region. Most of the communities are scattered, with small population sizes.

In Kintampo, the surveillance population numbered approximately 200,000 in 2011. The Kintampo HDSS site is a multi-ethnic area, and farming is the most important economic activity. Apart from the central area, few villages have electricity and most are reached by dirt roads. Access to health facilities is particularly challenging in Kintampo. One-third of pregnant women did not deliver in health facilities, according to our situation analysis.

In Navrongo, the surveillance population numbered approximately 153,000 in 2011. Navrongo is the first area where the Community-based Health Planning and Services (CHPS) program was launched in Ghana. In that context, Community Health Officers (CHOs) contribute to improving the health status of the rural community. Almost 90% of women delivered at health facilities and received PNC within 48 hours of giving birth, according to our situation analysis.

[figure not shown]

**Figure 1** Map of Health Research Centers

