### ***Implementation impact outcomes***

The implementation impact outcomes are 1) acceptability of CoC card utilization and 2) feasibility of improved PNC rates within 48 hours postpartum by mothers' retention at the health facility or by home visits. These outcomes are to be compared before and after the intervention.

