The trained DHMT/SDHT staff members will supervise the trained health service providers through a regular monthly supervision in their catchment areas. The aim is to visit each health facility at least once a month to directly observe health providers' service provision. A standard sheet will be developed to support supervision, with space in which to record activities and issues raised.

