#### ***(B-2) Postnatal care by home visits***

Functional CHOs will be encouraged to visit mothers and babies for PNC within 48 hours postpartum. Similar to the B-1 intervention, the aim of this intervention is to improve the within-48-hours-postpartum PNC rate for mothers and neonates. The implementation period will run from **October 2014 to December 2015**. The intervention is composed of two steps. The first step is delivery notification: in case of home delivery, Community Health Volunteers (CHVs), Community Key Informants (CKIs) or Traditional Birth Attendants (TBAs) will inform the CHOs about the labor or delivery. In the case of facility

delivery, when a woman has left the facility before the first PNC, SBAs will convey that information to CHOs so that they can visit the woman at home for PNC. The second step is PNC by home visits: CHOs will visit mothers and their neonates for PNC within 48 hours of delivery for women who delivered at home. If a woman delivers at a health facility but does not receive PNC within 48 hours, CHOs will visit her according to the information obtained from the health facilities. Approximately 8,750 women are estimated to be using this service.

The PNC by home visits will be conducted by functional CHPS zones with compounds. Targeted CHPS coverage is 50% of the total area. The estimated number of CHPS zones is 17 in Dodowa, 18 in Kintampo, and 21 in Navrongo. Delivery information will be communicated to the functional CHPS compounds via CHVs, CKIs, and TBAs. These messengers will receive two Ghana cedis (approximately 1 USD) per labor or delivery message conveyed as part of their communication fee. The money will be paid from the Ghana EMBRACE Implementation Research project budget. The women will be advised to visit health facilities for PNC on the seventh day after delivery. If the women do not come to the health facility, the CHOs will visit their homes to provide PNC service, as part of their routine follow-up duties.

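### The implementation outcome on 48-hour PNC draws on facility supervision with no stated denominator; unless all births are counted, the after rate would be overstated and not comparable with a household-survey baseline

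*Protocol*

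**What the plan says.** Under Implementation impact outcomes, the second outcome is the "feasibility of improved PNC rates within 48 hours postpartum", achieved through facility retention or home visits. The first is acceptability of the CoC card. For both, "These outcomes are to be compared before and after the intervention".

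Impact Evaluation separates two strands. The intervention package is assessed through the baseline and evaluation surveys, with mother-level data that include PNC within 48 hours. For the implementation strand, "a set of data and supporting information will be collected during the supervision by the DHMT/SDHMT". These data cover card distribution and actual card users, "as well as uptake of PNC within 48 hours postpartum, either by retention of mothers at the facilities or by home visits". The only other implementation source named there is qualitative.

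Section A-2 describes the supervision: "The aim is to visit each health facility at least once a month to directly observe" how providers deliver services. Section B-2 brings a home birth to the community health officer through a volunteer, key informant or traditional birth attendant, and home visits are made by functional CHPS zones with compounds. "Targeted CHPS coverage is 50% of the total area".

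On delivery place, Study Setting says of Kintampo: "One-third of pregnant women did not deliver in health facilities". For Navrongo it says that almost 90% delivered in a facility and had PNC within 48 hours.

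**The concern.** A facility visit can see women who came to the facility and births that were reported to its staff. A home birth that was never notified appears in neither group, and that mother is among those least likely to have had PNC within 48 hours. The section on the EMBRACE intervention itself links low uptake to the difficulty of reaching a facility after a home delivery.

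If the rate is formed among women known to providers, such women drop out of the denominator and the rate rises. The rise is larger where home delivery is more common, so it would differ between sites whose contexts the trial means to study.

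The before/after design adds to this. The supervision described here follows providers trained in August 2014, just before the intervention, and the only baseline instrument described is a household survey. A household-based before value set against a supervision-based after value could show improvement with no change in care. The card-use figure has the same weakness, because a woman with no contact is not seen as someone without a card.

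**Working it through.** The Protocol gives no rate, target or denominator for this outcome, so there is no figure to reproduce. What follows illustrates size under stated assumptions.

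**Inputs from the Protocol**
- Home-delivery share h: 1/3 (Kintampo), and about 10% as an upper bound for Navrongo (Study Setting).
- CHPS coverage: 50% of the area (B-2).

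**Assumptions not in the Protocol**
- 50% of area equals 50% of home births.
- Every home birth inside a functional zone is notified; none outside is seen, and none outside has PNC within 48 hours.
- PNC uptake after facility birth (f) and after home birth inside a zone (g): 80% and 50%, or 90% and 80%.

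**Formulas**
- Visible share V = (1 − h) + 0.5h
- True rate T = (1 − h)f + 0.5h·g
- Recorded rate R = T / V
- Overstatement R − T = R × (1 − V)

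**Results**

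| h | V | f, g | T | R | R − T |
|---|---|---|---|---|---|
| 1/3 | 0.833 | 80%, 50% | 0.533 + 0.083 = 61.7% | 74.0% | 12.3 |
| 1/3 | 0.833 | 90%, 80% | 0.600 + 0.133 = 73.3% | 88.0% | 14.7 |
| 10% | 0.950 | 80%, 50% | 0.720 + 0.025 = 74.5% | 78.4% | 3.9 |
| 10% | 0.950 | 90%, 80% | 0.810 + 0.040 = 85.0% | 89.5% | 4.5 |

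Because R cannot exceed 1, the overstatement cannot exceed the unseen share 1 − V: 16.7 points at h = 1/3 and 5 points at h = 10%. The two true rates at 10% lie below the almost 90% reported for Navrongo. Since the bound is 5 points, higher uptake would hardly change the gap.

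**Second model, without the area assumption.** Let r be the share of home births reached, all of whom receive PNC. Then T = (1 − h)f + h·r and R = T / [(1 − h) + h·r].
- h = 1/3, f = 80%, r = 50%: T = 70.0%, R = 84.0%, gap 14.0 points.
- h = 10%, same f and r: T = 77.0%, R = 81.1%, gap 4.1 points.
- Over f from 60% to 90% and r from 0 to 100%, the gap runs from 0 to 30 points at h = 1/3 and from 0 to 9 points at h = 10%. It is zero when every home birth is reached.

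In both models the gap is zero if the denominator is all births.

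**The case against.** A reader might infer that the Protocol has fixed a biased rate, or that the case for scale-up would rest only on women already in contact with services. The document supports neither.

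- **No denominator is stated.** Supervision could supply counts that are then divided by survey or HDSS births, which would remove this bias. The supervision sheet is still to be developed, and a SAP may define the rate. This stands, and it makes the overstatement conditional. But the Protocol does fix the source, and supervision data alone cannot later recover women whom they never recorded.
- **A mother-level rate already exists.** PNC within 48 hours is a secondary intervention outcome, based on individual data and compared between arms. This stands: that outcome does not depend on supervision.
- **Home births outside functional zones lie outside B-2 by design.** This stands too. How well B-2 works where it operates is a fair process question, but it is not the PNC rate among all deliveries.
- **Women who deliver at home are not wholly unknown.** Cards are given at first contact, including antenatal care, and notified home births reach the health officers. This is correct and narrows the gap. Still, no route is described by which an un-notified birth, and the absence of early PNC after it, would enter supervision data.
- **The sizes rest on assumed uptake and on treating area as births.** Agreed; they are illustrative.
- **No formal comparison between sites is planned.** Study Setting speaks only of evaluating feasibility in different contexts. A bias that varies by site would still colour that evaluation.

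**Conclusion.** The point holds in conditional form. The Protocol takes 48-hour PNC uptake and card use for its implementation outcomes from a source described as facility visits, states no denominator, and requires a before/after comparison whose only described baseline instrument is a household survey. Unless all births form the denominator, the after rate would be conditional on contact with services and overstated, and the change from baseline could partly reflect the change of source.

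Under the first set of assumptions the overstatement is about 12 to 15 points at one-third home delivery and about 4 points at 10%. It depends on assumed uptake and on the share of home births that providers learn of. The secondary between-arm outcome is not affected. The matter deserves correction because this is one of only two implementation outcomes in a hybrid trial, but it does not touch the primary outcome.

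**What to change.** - Compute the second implementation outcome from mother-level survey data among all eligible resident deliveries. Use the same denominator at baseline and evaluation, and split by route of first PNC: facility retention, home visit, other, none.
- Compute the share of women holding a card in the intervention arm from the same evaluation data.
- Keep supervision data as process counts: cards issued, notifications received, visits made.
- Reconcile who enters the evaluation survey. Impact Evaluation admits mothers who had at least some MNCH care in the intervention period, whereas Study Population defines eligibility by gestation and time since delivery, with no such condition. Read literally, the first would again drop women with no contact; they must stay in the denominator.
- Use HDSS births to check that the denominator is complete. The Protocol does not say that HDSS records the timing of PNC, so HDSS alone cannot supply the rate.

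The cost is at most one added survey item on route of first PNC and card holding, because 48-hour PNC is already collected for each mother. The rate obtained may be less favourable.
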